#### Acceptability

The acceptability of the study will be largely informed by the qualitative interview following the intervention.

Participants will be interviewed about their experience of the intervention via telephone approximately 1 week after they have completed the study. The interviews will be semistructured and follow a predefined schedule (see table 2). The interview will be centred around the acceptability of the intervention, but also aspects of the study. To this end, the interview will ask questions about motivations for taking part and expectations, how informed they felt before taking part, their experience of completing the questionnaires and having physiological measures taken, and their experience of the intervention itself. Some questions will also ask participants how they have felt since the intervention. Participants will then be given a chance to provide any other feedback or thoughts on taking part in the study. The audio from the interviews will be recorded and then transcribed.

**Table 2 T2:** Interview schedule for qualitative interviews

Information and consent	1. Were there any parts of the information sheet that were difficult to understand?
	2. Did any part of your participation feel unexpected, based on what you were told in the information sheet?
Motivations for participating	3. What motivated you to participate in the study?
	4. What did you know about osteopathy before taking part?
Outcome measures—questionnaires	5. Were there any questions or words on the questionnaires that were difficult to understand?
	6. What was your experience like filling out the questionnaires?
Outcome measures—physiological	7. What was your experience of having an ECG and blood pressure taken?
	8. What was your experience of doing a heartbeat detection task?
Intervention	9. Did you feel that the practitioner adequately explained the procedures to you?
	10. What could have gone better during the session?
	11. Did you take anything useful away from the session or learn anything new?
	12. How likely are you to visit an osteopath again or seek similar treatments after this?
Closing points	13. What else could you tell us about your experience of taking part in this study?

Analysis of the data will be conducted using reflexive thematic analysis.^37^ This involves initially familiarising oneself with the transcripts and then coding the data. Codes are then collated into themes. From here, themes are refined and categorised into main themes, midlevel themes and subthemes. Themes will then be discussed in terms of their strength. That is an indication will be provided of whether themes were common across many participants’ accounts, or only mentioned by a few. It is hoped that by employing qualitative methods, a richer account of the acceptability of the study and intervention to participants can be obtained.

The practitioners will also be interviewed about their experience of delivering the intervention. This interview will also be thematically analysed, and the resulting themes explored.

Additionally, any adverse events occurring during the study will be logged using the adverse events report form (AERF; this can be found in online supplemental material 2).

10.1136/bmjopen-2023-071680.supp2Supplementary data

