#### Additional outcomes

Demographic information will also be collected from participants relating to their gender, age and ethnic background. Although participants will have been screened for chronic pain, they will be asked whether they are currently or have recently been experiencing any neck pain or headaches. This is to inform the clinician about any problematic body areas, which may, therefore, be avoided in the intervention. The participants should be presenting as pain-free due to the initial screening process, but this is still a necessary safety measure. Participants will be excluded from the analysis if they present with neck pain or headaches.

Participants will also be asked whether they are currently receiving any mental health treatment. They will be asked whether they are currently taking any antidepressants or other related prescribed medication for mental health issues. Participants will also be asked whether they have recently attended or are currently attending any form of talking therapy or other psychotherapy. Participants’ prescription medication or psychotherapy status will not exclude them from the study. However, this will again be entered as a covariate if several participants report that they are receiving these psychological treatments.

Lastly will be the noting of any adverse events that occur during the intervention or study period. These will be filled out by the practitioner using the AERF and collected by the researcher if occurring during the intervention. If participants contact the researcher after the intervention regarding an adverse event, then this will be logged by the researcher.

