### Harms

The osteopathic practitioner will inform the participants about the general potential common adverse effects of osteopathy namely some stiffness and soreness in the days following the intervention, and rare adverse events including tissue damage,^51^ in line with informed consent processes. The osteopathic practitioner will record any adverse effects on the day the intervention is received (that occur during or immediately after the intervention) in the AERF (see online supplemental material 2). Participants will also be advised to contact the PI [name] by telephone if they have any concerns or adverse events following the intervention in subsequent days after the intervention was received. If such events are reported, these will again be reported by [name] in the AERF. Any adverse events or harms that are ranked highly on severity will be reported to the ethical committee. This includes any adverse events that, for example, require hospitalisation.

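### The 1-week interview schedule omits the promised question on how participants have felt since the session, so delayed adverse effects are captured only passively

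*Protocol article*

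**What the plan says.** All references are to the protocol article.

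- **Interview.** Under Acceptability, each participant is interviewed by telephone about 1 week after completing the study, in a semistructured form that follows the predefined schedule in Table 2. The text states: "Some questions will also ask participants how they have felt since the intervention".
- **Expected harms.** Under Harms, participants are told of the "common adverse effects of osteopathy namely some stiffness and soreness in the days following the intervention".
- **Recording on the day.** Also under Harms, the practitioner records "any adverse effects on the day the intervention is received (that occur during or immediately after the intervention").
- **Recording afterwards.** Harms continues: "Participants will also be advised to contact the PI" by telephone about concerns in the following days, and "If such events are reported, these will again be reported by" the named person on the AERF. Additional outcomes names a different recipient: "If participants contact the researcher after the intervention regarding an adverse event, then this will be logged by the researcher".
- **General commitment.** Acceptability also says that "any adverse events occurring during the study will be logged using the adverse events report form".

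**The concern.** The effects that the plan itself calls common are expected after the period in which anyone is assigned to look for them. Once the participant has left, an event is recorded only if he or she decides that it is worth a call. Mild soreness is the kind of effect that people tend not to report unprompted.

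The plan already has a contact with every participant at the right time, and its text says that this contact covers how they have felt since. The schedule that the interviewer will follow does not carry that through.

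Acceptability is a primary outcome, the interview is its main source, and the adverse-event log is described in the same section. Participants are screened to be free of pain, so new soreness after treatment is directly informative about tolerability for the later trial. A low count from passive reporting could be read as good tolerability when it may only mean that nobody asked.

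**Working it through.** No figure in the protocol can be reproduced here; the check is a comparison of the sections.

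**1. The interview text against Table 2.**

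- Items 1–2: information sheet and consent.
- Items 3–4: motivation and prior knowledge of osteopathy.
- Items 5–6: the questionnaires.
- Items 7–8: ECG, blood pressure and the heartbeat task.
- Items 9–12: the practitioner's explanation, what could have gone better in the session, anything useful taken away, likelihood of further visits.
- Item 13: anything else about taking part.

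Items asking how the participant has felt since the session: 0 of 13. Items asking about adverse effects: 0 of 13. The text promises more than one question of the first kind. The numbering runs from 1 to 13 without a gap, so there is no sign of a lost row.

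**2. When events are expected against when they are sought.**

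- Expected: the days after the session (Harms).
- Actively recorded: during the session and immediately after it, on the same day (Harms).
- Later days: on the participant's initiative, in both Harms and Additional outcomes.
- Scheduled contact in the later period: the telephone interview only (Table 3, follow-up at 1 week).
- Link from that interview to the AERF: none stated.

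The general commitment to log every event during the study therefore has no active means of finding events after the first day.

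**3. Who receives later reports.** Harms says the PI; Additional outcomes says the researcher. Implementation and Blinding describe the person who recruits and collects data as the blinded outcome assessor, who also analyses the data and learns the allocation only once the analysis is complete. Data management gives access to the outcome assessor alone, and Confidentiality and Access to data give it to a single researcher. Together these suggest that the researcher is the blinded analyst, although no section says so outright.

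**4. What a zero count could support.** Inputs: 32 participants (Sample size) in four equal arms, so 32/4 = 8 per arm. If every participant is asked and none reports an event, the one-sided upper 95% bound on the event rate is 1 − 0.05^(1/n):

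- all participants: 1 − 0.05^(1/32) = 8.9%;
- one arm: 1 − 0.05^(1/8) = 31%.

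These bounds do not measure the undercount. They show that even complete ascertainment supports only a loose statement about each arm. Without a known number asked, a zero count does not support even that.

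**The case against.** The strongest reply is that the plan is not as closed as it looks. It commits to logging any adverse event during the study. The interview is semistructured, and items 2 (anything unexpected), 11 and 13 give room for a participant to mention soreness. The AERF is in a supplement that is not shown and may contain follow-up prompts. All of this is fair, and a reader who inferred that a delayed effect can surface only through a telephone call would go too far. What stands is narrower: no listed item asks about later effects, and nothing says that an interview mention reaches the AERF. Chance mentions also give no denominator.

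Three stronger readings are tempting and not supported.

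- **That the undercount drives a go/no-go decision.** The document contains no such rule. Its feasibility thresholds concern responses, eligibility and measurement time; none uses adverse events.
- **That the undercount can be given a size.** That would need the true rate of delayed soreness and the share of affected people who call. The document gives neither.
- **That the reporting route breaks the blind.** The identity of the researcher is inferred. Outcome measurement ends straight after the session (Table 3), so a later call cannot bias it; only the blinding of the analysis could be affected. Soreness alone does not identify the arm, since all four arms are manual treatment. The risk lies in what else the participant says on the call.

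**Conclusion.** The point holds as an internal inconsistency with a practical consequence. The Acceptability text and Table 2 disagree on whether participants are asked how they have felt since the session. If Table 2 is followed as printed, delayed effects are captured passively, in the period when the plan expects its common ones. The count is then likely to be too low, by an amount that cannot be estimated from the document. This rests on two assumptions: that interviewers keep to the printed items, and that the AERF is a recording form without solicited follow-up, which is how the text describes its use.

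The disagreement between Harms and Additional outcomes on who receives later reports is a smaller point that needs reconciling. The risk to the blinded analysis is a reason to choose one route over the other, not an established failure of blinding.

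**What to change.** 1. Add one item to Table 2, in fixed wording and asked of every participant at the 1-week call: any pain, stiffness, soreness, headache or other problem since the session, with onset, severity and whether it has resolved.
2. State that the answers are entered on the AERF.
3. Report solicited events with the number of participants asked as denominator, separately from spontaneous reports. If zero-event bounds are given, label them as one-sided 95% bounds.
4. Reconcile Harms and Additional outcomes to one route for later reports, preferably the PI.
5. Keep the adverse-event answers from the interview away from the analyst until the blinded analysis is complete. The document does not say who conducts the interviews; if it is the analyst, someone else should ask this item.

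**Cost.** One question in a call already scheduled, and probably a minor notification to the ethics committee. The study began on 20 December 2022, so anyone already interviewed will not have been asked. Those participants must be reported separately, and ascertainment will be mixed. The adverse-event count will rise, which should be explained as the result of asking.

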#### Psychological outcomes

These measures are intended to provide some initial data on the potential utility of the intervention for outcomes such as depression, anxiety and stress, psychological flexibility, and interoceptive awareness. They will be collected during preintervention and postintervention and any changes will be analysed.

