### Objectives

This study aims to investigate the feasibility and acceptability of four osteopathic interventions for adults with mild to moderate mental health symptomatology. A secondary aim is to evaluate the influence of these four interventions on physiological factors including HRV and interoception. The study will aim to evaluate their effectiveness in improving psychological outcomes including depression, stress, anxiety, negative affect (NA) and psychological flexibility. It is first hypothesised that the interventions will be feasible and acceptable to participants. It is also hypothesised that the interventions will induce psychophysiological relaxation by significantly increasing HRV and improving IAc. No specific predictions are made about blood pressure (BP) as data on this is only being collected to check that we are within safe BP bounds, that is, for participant safety. A final hypothesis is that the four interventions will lead to similar improvements in depression, anxiety, stress and NA.

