### Interventions

Participants will receive one of four interventions based on osteopathic techniques. All four interventions will consist of a single session lasting approximately 30 min. The interventions are being delivered by two male osteopaths, one with 17 years of practice experience and one with 3 years of practice experience. The interventions will be as follows: (1) articulation and HVT techniques, (2) STM, (3) CST and (4) a combination of all three techniques. A summary of the intervention protocols can be found in table 1.

**Table 1 T1:** Summary of the four intervention protocols and procedures

For all	30 min appointment Clinical findings, intervention, consent and adverse events (separate form to use if they do) recorded in participant individual form	Duration
Articulation/HVT group	Observation+AROM (standing or sitting)+clinical examination for SD (sitting, prone or supine) Techniques: SD found: HVT to the area unless contraindicated (info on BP/HA) No SD found: HVT TSp and ribs Articulation of hips in extension	10 min 20 min
Soft tissue group	Full body, slow and superficial Prone: upper/mid/lower back upper buttocks hamstrings calves Supine: Neck incl. suboccipital muscles Shoulders Pectoral muscles Arms Quadriceps Feet	15 min 15 min
Cranial group	Looking for stiffness, asymmetry and tenderness on: Sacrum Head Dysfunction found: myofascial release technique (10 min/area); if no dysfunction found: functional techniques applied to each area (10 min/area) 3. CV4	10 min 10 min 10 min
Combined group	Observation+AROM+clinical exam for SD HVT TSp Soft tissue upper and lower back prone CV4 and suboccipital release	9 min 7 min 7 min 7 min

AROM, active range of movement; BP, blood pressure; CV4, Compression of the Fourth Ventricle technique; HA, headache; HVT, high velocity thrust techniques; SD, somatic dysfunction; TSp, thoracic spine.

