##### Mental health

###### Depression, Anxiety and Stress Scale

The DASS^38^ is a self-report measure made up of 21 items with three subscales that measure depression, anxiety, and stress. The DASS will also be used as a screening tool to identify eligible participants in terms of the severity of mental health symptoms. Examples of items include ‘I couldn’t seem to experience any positive feeling at all’ for the depression scale, ‘I felt I was close to panic’ for the anxiety scale and ‘I found myself getting agitated’ for the stress scale. These are then rated on a four-point Likert scale ranging from 0 (never) to 3 (almost always). Higher scores indicate higher levels of depression, anxiety and stress. The subscales have good internal reliability as measured by Cronbach’s alpha coefficients (α), which are 0.88 for depression, 0.82 for anxiety and 0.90 for stress, as well as 0.93 for the total score.^39^

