###### Self as Context Scale

The Self as Context Scale (SACS)^42^ uses 10 items to measure self-as-context, one of the acceptance components of psychological flexibility. Self-as-context can be described as a transcendent sense of self, where the individual is able to distance their ‘noticing self’ from internal thoughts and feelings. The SACS has two subscales: (1) centring, for example, ‘when I am upset, I am able to find a place of calm within myself’, and^1^ transcending, for example, ‘As I look back upon my life so far, I have a sense that part of me has been there for all of it’. Items are then rated on a seven-point Likert scale from 1 (strongly disagree) to 7 (strongly agree). Higher scores on the subscales indicate higher levels of centring, and transcending and a higher total score indicates greater levels of self-as-context. The SACS has good internal reliability with Cronbach’s α of 0.81 for centring, 0.78 for transcending and 0.81 for overall SACS score.^42^

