### Participant timeline

See table 3 for the participant timeline.

**Table 3 T3:** Participant timeline

Activity/ assessment	Approx. time to complete	T_-1_ Prestudy screening/ consent	T_0_ Prestudy randomisation	T_1_ Preintervention	T_2_ Intervention	T_3_ Postintervention tests	F_1_ Follow-up 1 week
Informed consent	5 min	X					
Screening with DASS	5 min	X					
Randomisation	15 min		X				
Baseline assessment— questionnaires	15 min			X			
Baseline assessment— physiological	15 min			X			
Intervention	30 min				X		
Postintervention questionnaires	15 min					X	
Postintervention physiological	15 min					X	
Telephone interview	30 min						X

DASS, Depression Anxiety Stress Scale; F, follow-up; T, timepoint.

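### DASS, AAQ-II, SACS and MAIA-2 are repeated only about 45 to 60 minutes after baseline, so their pre-post change cannot be read as improvement in symptoms, flexibility or interoceptive awareness

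*Protocol article*

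**What the plan says.** **Timing.** Under Psychological outcomes, the article says of the questionnaires: "They will be collected during preintervention and postintervention and any changes will be analysed". Table 3 (Participant timeline) places them at T1 and T3, on either side of the treatment. Under Interventions: "All four interventions will consist of a single session lasting approximately 30 min". The only later contact is described under Acceptability: "Participants will be interviewed about their experience of the intervention via telephone approximately 1 week after they have completed the study". Table 3 lists no questionnaire at that contact (F1).

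**Instruments, as the article describes them.**
- DASS: "These are then rated on a four-point Likert scale ranging from 0 (never) to 3 (almost always".
- AAQ-II: seven-point rating of how true general statements are, from never to always.
- SACS: agreement with general self-statements such as "As I look back upon my life so far, I have a sense that part of me has been there for all of it".
- MAIA-2: six-point frequency rating, never to always, of habitual bodily awareness.
- PANAS-SF: the extent to which states such as feeling upset or inspired have been felt.

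**Use of the scores.** Objectives sets a secondary aim of evaluating effectiveness on depression, stress, anxiety, negative affect and psychological flexibility, and adds: "A final hypothesis is that the four interventions will lead to similar improvements in depression, anxiety, stress and NA". The Discussion paragraph of the Abstract promises effect sizes as preliminary evidence of benefit, and says the results will inform a later randomised trial. Statistical methods fits one pre-post by arm ANCOVA per questionnaire. Additional analyses correlates pre-post change in HRV with pre-post change in DASS.

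**The concern.** A scale that asks how often a symptom occurs, or how true a statement is of one's life in general, summarises a period or a disposition. Between the two administrations the participant has only baseline physiological testing and one treatment session. That gives almost no new experience on which to revise such an answer.

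Scores may still move. But participants know what treatment they had (Blinding), and there is no control group (Strengths and limitations). A shift could therefore reflect current mood, memory of answers given an hour earlier, or expectation, and the design cannot separate these from a real reduction in symptoms.

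At stake are the effectiveness part of the secondary aim, the depression, anxiety and stress components of the final hypothesis, and the effect sizes that a full trial would inherit. The limitations listed in the article cover low power and the missing control group but not this point, so readers are not warned of it.

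**Working it through.** The article gives no figure for the interval between administrations, so there is none to reproduce. It follows from Table 3.

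**Inputs (Table 3).** "Baseline assessment— questionnaires 15 min"; "Baseline assessment— physiological 15 min"; intervention 30 min; post-intervention questionnaires 15 min; post-intervention physiological measures 15 min. Write Q = 15 (questionnaires), P = 15 (physiology), I = 30 (intervention).

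**Is it one visit?** No clock time is stated, but three places point the same way:
- Blinding has the assessor finish the baseline measures and leave the room, whereupon treatment starts.
- Implementation has the osteopath open the envelope on the study day itself.
- Acceptability dates the interview from completion of the study, and Table 3 shows only the interview after T3.

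**Interval between the two questionnaire administrations (min).**

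| Order within the visit | End to start | Start to start |
|---|---|---|
| Questionnaires first both times (Table 3 order) | P + I = 15 + 30 = 45 | Q + P + I = 15 + 15 + 30 = 60 |
| Physiology first at baseline, questionnaires first afterwards | I = 30 | Q + I = 15 + 30 = 45 |
| Questionnaires first at baseline, physiology first afterwards | P + I + P = 15 + 30 + 15 = 60 | Q + P + I + P = 15 + 15 + 30 + 15 = 75 |
| Physiology first both times | I + P = 30 + 15 = 45 | Q + I + P = 15 + 30 + 15 = 60 |

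In Table 3 order the gap is 45 to 60 min, depending on how it is counted. No order takes it beyond 75 min.

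**Interval set against response format.**

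| Scale | What the answer summarises | Can a T1-T3 change be read as change in the construct? |
|---|---|---|
| DASS | Frequency of symptoms | No |
| AAQ-II | General truth of statements | No |
| SACS | General view of oneself | No |
| MAIA-2 | Usual bodily awareness | No |
| PANAS-SF | Extent of felt states | Could respond within a session; not challenged here |

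Four of the five questionnaires are affected. Within the final hypothesis, depression, anxiety and stress (DASS) are affected and negative affect (PANAS-SF) is not. Psychological flexibility (AAQ-II, SACS) appears in the aim but not in that hypothesis.

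**The case against.** **It is a feasibility study and these are secondary outcomes.** This stands, and it limits the severity. The Outcomes section makes feasibility and acceptability primary, Psychological outcomes offers the scores only as initial data, and no primary outcome depends on a change in DASS. It does not remove the point, because Objectives speaks of effectiveness and the Abstract promises effect sizes.

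**The interview covers the following week.** Acceptability does say that some questions will ask how participants have felt since treatment. That is qualitative information and gives no score to set against baseline.

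**A 1-week score has its own problem.** This also stands. Participants are selected on a DASS band (Recruitment) and there is no untreated arm. Within-group change from T1 to F1 would therefore include natural fluctuation, a week of outside events and possibly regression to the mean. Taking DASS out of T3 would also break the planned same-visit correlation with HRV change. The fix has to allow for both.

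**Stronger readings to avoid.**
- A reader might infer that the scores cannot move, or that the T3 data are worthless. The documents do not support that: immediate mood can colour the answers. The limit is on interpretation.
- A reader might want to express the interval as a percentage of a recall period. The article states no recall period for DASS, and it describes AAQ-II, SACS and MAIA-2 without any time window, so such a percentage has no basis.
- A reader might infer that single-visit collection empties the missing-data criterion under Feasibility. That criterion concerns completion of the questionnaires, not retention, and items can be skipped within one visit.

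**Conclusion.** The point holds as an interpretive limit on a secondary aim. As timed, T1-T3 change on DASS, AAQ-II, SACS and MAIA-2 is an immediate post-session response. It should not be reported as improvement in depression, anxiety, stress, psychological flexibility or interoceptive awareness, nor carried into a full trial as an effect size for them.

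The primary outcomes, PANAS-SF, the heartbeat task and the HRV measures are untouched. A reader might infer that the study fails its purpose; it does not, because feasibility and acceptability do not rest on these scores.

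The conclusion rests on two things: the same-visit timing, inferred from Table 3, Implementation and Blinding; and the response formats as the article describes them. It needs no assumption about recall windows. Severity: should be fixed.

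**What to change.** 1. Keep all T3 questionnaires, so that the same-visit correlations with HRV change remain possible, and label their change as immediate post-session response.
2. For participants still to be treated, add DASS, AAQ-II, SACS and MAIA-2 as an online form at the existing 1-week contact (F1), completed before the interview.
3. Use T1-F1 change, compared between the randomised arms, for the symptom and flexibility effect sizes. Report the F1 completion rate as a feasibility result.
4. State that within-group T1-F1 change is uncontrolled and open to regression to the mean after selection on DASS. The between-arm comparison contrasts active treatments only, with 32/4 = 8 participants per arm at most, so it will be imprecise.
5. If F1 scores cannot be added, restate the secondary aim and final hypothesis as immediate affect and physiological response, and do not report T3 change on the four scales as effectiveness.

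**Cost.** Items 2 to 4 take about 15 min per participant (judging by the 15 min that Table 3 allows for the questionnaires) and an ethics amendment. The study began on 20 December 2022 and is due to finish by 1 August 2023, so participants already treated will have no F1 scores. Some F1 forms will also go unreturned. Item 5 needs only a change of wording.
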